## Abstract

**Background::**

The bloodletting device has been used by many institutions for about 100 years. Many patients feel fear from the pain caused by applying the bloodletting device for treatment. We used bloodletting device using the principle of “prestimulation neurodisturbance,” which can mask the subject undetectable for pain. In this study, we will investigate pain of bloodletting device during blood collection and will identify the safety of the device.

**Methods::**

This study will be a randomized, controlled, double-blind, and matched-paired-designed clinical trial. Four groups, RTLC, LTRC, RCLT, and LCRT (T = test device, C = control device, L = left, R = right), will be randomly allocated. Total duration of the clinical trial will be 3 months. The subjects will be performed from 1 to 3 times only on the day of the procedure. The primary outcomes will be measured using pain visual analog scale score and the secondary outcomes will include verbal rating scale and the time at which the pain disappears after blood collection (second), the total number of “nonbleeding” cases and subjects, the number of “blood collection failure” and subjects, the presence of “delayed hemostasis,” and the number of subjects. Repeated-measure analysis will be used to measure primary efficacy based on full analysis set.

**Discussion::**

This study has limited inclusion and exclusion criteria and a well-controlled intervention, and it will be the first randomized controlled trial to investigate pain of bloodletting device using the principle of “prestimulation neurodisturbance.” This study provides insights into the underlying mechanisms of the pain-reducing effect of the developed bloodletting device and will lay the groundwork for further studies.

## Introduction

1

The bloodletting device has been used by many institutions for about 100 years but mostly by hospitals that practice western medicine and Korean medicine. Bloodletting devices are used for various purposes, such as blood collection for examinations or blood collection to relieve muscle tension. In our Korean medicine hospital, many patients fear the pain caused by applying the bloodletting device for the treatment of a medical condition.

Improvements have been made in the mechanical elements of existing bloodletting devices, such as thinning, smoothing, and shortening the needle. However, since the thickness of the skin is different for each person, there is a disadvantage that the depth of the needle cannot be precisely adjusted.

In the present study, the principle of “prestimulation neurodisturbance” was used; that is, if the area is first stimulated with another stimulus before the needle enters the skin, the nerves in the femoral cortex are disturbed. When the nerve is disturbed, the needle pierces the skin quickly and falls out, masking the pain.^[1]^ Therefore, we designed a study protocol to investigate the pain associated with use of a new bloodletting device by using a randomized, controlled, double-blind, and matched-paired-designed clinical trial.

## Materials and methods

2

### Study design

2.1

This randomized, controlled, double-blind, matched-paired clinical trial will compare the pain associated with use of 1 bloodletting device (ROAH-L-NO1) to that associated with a control device (LANZO 1.5). One hundred outpatients will be recruited from the Daejeon University Cheonan Korean Medicine Hospital through advertisements posted on bulletin boards in hospitals. Recruitment commenced in October 2019, and the trial is expected to end in December 2019. One hundred patients who meet the eligibility criteria for this study will be randomly assigned to groups A, B, C, or D. The intervention will begin on the day of the screening visit. Depending on the study group, 2 procedures will be performed, 1 for each participant's hand, in the order of the right and left hand labeled on the bloodletting devices according to the randomization code. The total duration of the clinical trial will be 3 months.

### Inclusion and exclusion criteria

2.2

The inclusion criteria are as follows: age, 19 to 64 years; ability to collect blood on the same finger of both hands; and patients who can communicate clearly and express their pain. The exclusion criteria are as follows: patients with blood clotting disorders, such as hemophilia or leukemia; those with structural disorders, such as defects or deformations of the blood collection area; patients who should avoid blood collection because of wounds and skin diseases; and those with sensory disorders in the area of blood collection, such as hemiplegia or peripheral nerve damage.

### Withdrawal and dropout

2.3

If the participant does not meet the inclusion or exclusion criteria or withdraws his/her consent, or if the participant's continued participation is judged as inappropriate, or if 3 instances of nonbleeding occurs on the same finger of a participant, he/she will be excluded from the study. The researchers will record the reason for any interruption in the intervention and whether each participant completed the study.

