### Intervention

2.6

The test device (ROAH-L-NO1) will be manufactured by Roahmed Medical Device Co. (Changwon, Republic of Korea), and the control device (LANZO 1.5) will be manufactured by GMMC Medical Device Co (Seoul, Republic of Korea). Both devices will be applied to the participants’ 3rd finger.

All eligible participants will receive a treatment according to the allocated group, RTLC, LTRC, RCLT, or LCRT, on the day of the screening visit. To maintain the double-blinded nature of the study, during the procedure, a screen will be placed between the participant and the operator. The operator will use the test and control devices on the participants on the outside of the screen, and participants will be indistinguishable to which hand the test device is assigned. The operator will practice using the randomized device on the 3rd finger of 1 hand of the participant. If blood is collected to the extent that the blood glucose level can be measured, it will be determined to be successful, and the 1st measurement will be completed. If no blood is collected, the participant will be checked to confirm no bleeding (“nonbleeding”), and treatment will be applied again after 10 minutes to determine whether blood collection is successful. When the total number of instances of nonbleeding is 3, no further procedure will be recorded, and “blood collection failure” will be recorded. The operator will check the participants’ state of hemostasis after bleeding, and if hemostasis does not occur within 3 minutes (“delayed hemostasis”), the participant will be checked again for complete hemostasis. If hemostasis does not occur for more than 10 minutes, the operator will check the participant for hemostasis abnormalities, and the operator will stop the clinical trial and seek medical attention for the participant. The secondary measurement will be performed 10 minutes after the primary measurement in the same way on the same area of the participants’ opposite hand. Participants will undergo the intervention from 1 to 3 times only on the day of the procedure.

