### Outcome measures

2.7

The primary outcome will be the VAS score, which will be assessed upon successful blood collection. The secondary outcomes will be the verbal rating scale (VRS) score and the time at which pain disappears after blood collection (second), which will be assessed upon successful blood collection. In addition, the total number of nonbleeding cases, number of blood collection failures, number of cases of delayed hemostasis, and number of participants will be counted. Participants’ data will be anonymized and coded by a specific program.

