### Statistical analysis

2.9

Statistical analysis will be primarily based on the principle of the full analysis set. Missing values will be analyzed by the last observation carried forward method. For each of the 2 devices, the VAS score and time at which the participant's pain disappears will be measured, and descriptive statistics will be presented as a mean, standard deviation, median, and minimum and maximum values. The analysis method for evaluation of the variables of efficacy will involve confirmation of the normality of the values and then comparison using the paired *t* test or Wilcoxon signed-rank test. The McNemar test will be used to analyze the VRS score, total number of nonbleeding cases, number of blood collection failures, number of cases of delayed hemostasis, and number of participants. The significance level will be set at *P* < .05 and the confidence interval at 95%. All statistical analyses will be performed using SPSS Statistics for Windows version 20.0 (IBM Corp, Armonk, NY).

If necessary, subgroup analyses of outcome variables, such as the demographic variables measured at baseline (e.g., sex, age, duration of illness, treatment expectation) can be performed. Safety assessments will be performed primarily by analyzing the frequency of adverse events and serious adverse events (SAEs) that researchers suspect to be related to treatment. The collected safety data will be summarized appropriately. All adverse events that occur will be listed with a detailed description. All SAEs will be recorded descriptively. The adverse events will be collected through patient symptom reporting and researcher observation. The frequency of each adverse event associated with or unrelated to the intervention will be recorded and analyzed using descriptive statistics. There is no intermediate analysis of this study, and the final decision regarding the completion of the clinical trial will be made by the PI.

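### Three nonbleeding sticks on one finger is both a reason for exclusion and the blood collection failure outcome, so first-hand failures have no pair for the planned McNemar test (minor, secondary outcome only)

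*Protocol article*

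**What the plan says.** - **Exclusion (section 2.3, Withdrawal and dropout):** "if 3 instances of nonbleeding occurs on the same finger of a participant, he/she will be excluded from the study".
- **Outcome definition (2.6, Intervention):** "When the total number of instances of nonbleeding is 3, no further procedure will be recorded", and blood collection failure is entered instead.
- **Outcome list (2.7, Outcome measures):** "number of blood collection failures, number of cases of delayed hemostasis, and number of participants will be counted". The abstract places these failures among the secondary outcomes.
- **Test (2.9, Statistical analysis):** "The McNemar test will be used to analyze the VRS score, total number of nonbleeding cases, number of blood collection failures".
- **Sequence of hands:** 2.1 says "Depending on the study group, 2 procedures will be performed, 1 for each" hand, and 2.6 says "The secondary measurement will be performed 10 minutes after the primary measurement in the same way" on the opposite hand. Neither section says what happens to the second hand when the first has failed.
- **Primary outcome (2.7):** "The primary outcome will be the VAS score, which will be assessed upon successful blood collection".
- **Missing data (2.9):** "Missing values will be analyzed by the last observation carried forward method".

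**The concern.** McNemar's test compares the two devices within a person and uses only the participants in whom exactly one device failed. It therefore needs a result from both hands. The exclusion rule removes a participant at the moment the outcome occurs. If that happens on the first hand, the second device is never applied and no later analysis decision can supply its result.

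At stake is the comparison of how often each device fails to draw blood. That matters beside a claim of less pain, since a device that hurts less but fails more often is not clearly better. The protocol chose a paired comparison for this outcome, and its own exclusion rule then discards part of the paired information.

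**Working it through.** The article gives no failure rate and no power figure for this outcome, so there is no stated figure to reproduce. The calculation shows what the rule costs over a range of assumed rates.

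**Inputs**
- From the article: 100 participants (2.1, 2.4); four equally allocated groups, two with the test device first and two with the control first, so about 50 per device order (2.5); significance at P < .05 (2.9).
- Assumed: failure rates fT (test) and fC (control) of 3% and 1%, 5% and 1%, or 8% and 2%; the two hands independent; no effect of order on failure.

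The 8% rate is an upper end. If sticks are independent, three misses in a row with probability 0.08 need a miss rate per stick of 0.08^(1/3) = 0.43.

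**Step 1. Unpaired first-hand failures.** Expected number = 50 × (fT + fC) = 2, 3 and 5.

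**Step 2. Discordant pairs (test failed only vs control failed only).**
- Both hands always attempted: 100·fT·(1 − fC) vs 100·fC·(1 − fT).
- As written, only when the failing device came second: 50·fT·(1 − fC) vs 50·fC·(1 − fT).

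| fT, fC | Both hands attempted | As written |
|---|---|---|
| 3%, 1% | 2.97 vs 0.97 | 1.49 vs 0.49 |
| 5%, 1% | 4.95 vs 0.95 | 2.48 vs 0.48 |
| 8%, 2% | 7.84 vs 1.84 | 3.92 vs 0.92 |

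The halving comes from the balanced order and holds at any failure rates.

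**Step 3. What the test needs.** With every discordant pair in one direction, the exact two-sided P is 2 × 0.5^5 = 0.0625 for five pairs and 2 × 0.5^6 = 0.031 for six. Fewer than six discordant pairs can never reach P < .05.

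**Step 4. Chance of at least six pairs, and power, by exact enumeration.**

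| fT, fC | At least 6 pairs: both hands → as written | Power: both hands → as written |
|---|---|---|
| 3%, 1% | 0.202 → 0.014 | 0.034 → 0.002 |
| 5%, 1% | 0.543 → 0.075 | 0.198 → 0.023 |
| 8%, 2% | 0.930 → 0.355 | 0.373 → 0.093 |

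**Step 5. Failure counts per device, as written.** A failure is still recorded against the device in use, so the expected counts are 50·fT + 50·fT·(1 − fC) vs 50·fC + 50·fC·(1 − fT):
- 2.99 vs 0.99 (3 vs 1 if both hands were always attempted)
- 4.98 vs 0.98 (5 vs 1)
- 7.92 vs 1.92 (8 vs 2)

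Hands attempted are 50 + 50·(1 − fC) for test and 50 + 50·(1 − fT) for control: 99.5 and 98.5; 99.5 and 97.5; 99 and 96. Count divided by hands attempted returns the assumed rates, for example 7.92 / 99 = 8% and 1.92 / 96 = 2%. The descriptive comparison survives; the paired test is what loses.

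**Step 6. Last observation carried forward.** Section 2.9 does not say the method would be applied across devices. If it were, a first-hand failure would be copied to a device that was never used. That adds a failure to that device's count and makes the pair concordant, so it restores no discordant pair.

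**The case against.** The strongest case against has four parts.

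1. **Another reading is possible.** Sections 2.1 and 2.6 can be read as stopping attempts on the failed finger and then going on to the other hand, and 2.3 does not say that exclusion comes before the second hand. This has some force, but 2.3 says the participant is excluded from the study and neither other section makes an exception to it. At best, operators have conflicting instructions for the same event, and that needs correcting too.
2. **The stop fits the population and protects participants.** Section 2.2 requires that blood can be collected from the same finger of both hands, and limiting sticks is sensible in a study of pain. The burden argument stands as a reason to keep a stop if the sponsor wants one. The entry criterion does not resolve the conflict, because the same event is still an outcome to be compared in pairs.
3. **Data handling belongs in the full protocol or analysis plan.** That is true of who stays in the full analysis set and how unpaired failures are tabulated. It does not cover a second-hand procedure that was never done.
4. **The effect is small.** This stands. Power is 37% at most under the assumed rates even with every hand attempted, the counts are nearly intact, and the primary outcome is untouched. It is why the point is graded minor.

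**Conclusion.** The concern holds and is minor. Followed as written, section 2.3 leaves every first-hand failure without a second-device result, and the expected discordant pairs for the failure comparison are halved. Under the assumed rates this is an expected 2 to 5 participants in 100, and exact McNemar power falls to between 0.2% and 9%, from between 3% and 37%. The halving rests on balanced order and no order effect. The power figures also rest on the assumed failure rates and on independent hands. If failures are rarer than assumed, the loss is smaller still.

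No bias toward either device is shown, because order is balanced. The failure counts per device change little, unless exclusion also means that recorded data are removed, which 2.3 leaves unclear. The paired VAS analysis is unaffected: VAS is taken only after successful collection, so a participant with a failed hand has no VAS pair under either rule.

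**What to change.** **Preferred**
- In 2.3, remove three nonbleeding sticks from the exclusion reasons.
- In 2.6, state that attempts stop on that finger only, that the failure is recorded against the device used, and that the opposite-hand procedure follows as planned if the participant agrees.
- In 2.9, state that these participants stay in the full analysis set for the failure outcome and that values are not carried from one device to the other.

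**If the stop is kept to protect participants:** say that first-hand failures are unpaired, and report failures per hand attempted for each device beside McNemar.

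**Cost:** wording in three sections and no extra participants. Under the preferred change, each participant whose first hand failed receives one to three further sticks on the other hand. With 2, 3 or 5 such participants expected, that is 2 to 6, 3 to 9 or 5 to 15 sticks in the whole trial. The fallback adds none.

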### Sample size calculation

2.4

The basis for calculating the subjects of this study was derived from the results of previous studies by Baxter et al.^[2,3]^Table 1 summarizes the evaluation results of those studies to estimate the effect size on the primary efficacy endpoint, visual analog scale (VAS) (100 mm).

**Table 1 T1:**

Evaluation results of the 2 studies (Baxter and Haliza).

The results were combined using the method described by Curtin, and the estimated magnitude of Buzzy effect on pain reduction during intravenous blood collection is summarized in Table 2.^[4–6]^

**Table 2 T2:**

Estimated magnitude of Buzzy effect on pain reduction.

Because the present study will proceed to the point of blood collection, not only the pain intensity is weaker than the previous study, but the duration and intensity of vibration are shorter or weaker than that of Buzzy effect. Therefore, the effect size on the pain reduction of the test device is thought to be smaller than that of Buzzy effect. In the design of the clinical trial, 4 sequences will be assigned, but since the 2 treatments and 2 periods are basically 2 × 2 cross designs, the formula for calculating the sample size corresponding to the design will be applied mutatis mutandis. Assuming that the effect size of the study device is n = (0.61 ÷ 2) ÷ 3,” the sample size (class 1 error *a* = 0.05; power 1 − *b* = 0.8) to be assigned to each device sequence will be as follows: 

Forty-three participants will be required for each treatment group. In addition, considering a 15% dropout rate, the number of participants required per treatment group will be 50. One hundred participants will be calculated as the total number of participants in this study.

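### Section 2.4: the printed effect size, (0.61 ÷ 2) ÷ 3 = 0.102, cannot give the stated 43 per device sequence at 80% power; the two must be reconciled

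*Protocol article*

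**What the plan says.** Section 2.4 (Sample size calculation, text after Table 2) argues that the test device should reduce pain less than the vibration device in the earlier studies, and assumes that "the effect size of the study device is n = (0.61 ÷ 2) ÷ 3". The error rates follow: "class 1 error *a* = 0.05; power 1 − *b* = 0.8". On the method, the section says that "since the 2 treatments and 2 periods are basically 2 × 2 cross designs, the formula for calculating the sample size corresponding to the design" is to be applied, with the result expressed per device sequence.

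The conclusions are "Forty-three participants will be required for each treatment group", then "considering a 15% dropout rate, the number of participants required per treatment group will be 50", and finally "One hundred participants will be calculated as the total number of participants in this study". Section 2.9 plans the matching within-participant analysis: "comparison using the paired *t* test or Wilcoxon signed-rank test".

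The displayed formula and the contents of Tables 1 and 2 are not visible in the text available. Section 2.4 states neither the sidedness of alpha nor the SD that standardises the effect.

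**The concern.** The effect size, alpha, power, design and resulting n stand together in one short stretch of text, and the n does not follow from the rest. An effect of about 0.10 SD is very small, and 43 per sequence is far too few to detect it with 80% power.

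This is the only justification shown for the sample size on the primary VAS endpoint, and the Discussion says that no pilot study was done. A reader who takes the section at face value would treat a null result as 80%-powered evidence against an effect of about 0.10 SD. The trial cannot supply that evidence.

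**Working it through.** **Inputs, all from section 2.4 unless noted**
- Printed effect size: (0.61 ÷ 2) ÷ 3 = 0.305 ÷ 3 = 0.1017.
- Alpha 0.05, taken as two-sided (assumption). Power 0.80.
- 2 × 2 crossover, n per device sequence. The four allocation groups form two device orders, test first or control first.
- Stated n: 43 per sequence (86 pairs), raised to 50 and 100 in total for 15% dropout.
- Paired analysis (section 2.9). The effect d is taken as mean difference ÷ SD of the within-participant difference (assumption).

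**Formulas (normal approximation)**
- n per sequence = (1.960 + 0.842)² ÷ (2d²) = 7.85 ÷ (2d²)
- power with N pairs = Φ(d√N − 1.96)

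**Reproducing the plan's 43**
- d = 0.305: 7.85 ÷ (2 × 0.0930) = 42.2, rounded up to 43. This matches.
- d = 0.30 (0.305 rounded): 43.6, which rounds up to 44.
- d = 0.1017: 7.85 ÷ (2 × 0.01034) = 379.7, so 380 per sequence, about nine times the stated figure.

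**Other conventions at d = 0.1017, to see whether any returns 43**

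| Convention | n required |
|---|---|
| One-sided alpha, SD of the difference | 299.1, so 300 per sequence |
| Two-sided, within-subject SD scale | 759.4, so 760 per sequence |
| Two-sided, parallel two-arm formula | 1,519 per arm |

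None comes close. If 0.1017 were on the SD of a single measurement, the SD of the difference would be SD × √(2(1 − ρ)), and n per sequence would be 7.85 × (1 − ρ) ÷ d². Setting this to 43 gives 1 − ρ = 43 × 0.01034 ÷ 7.85 = 0.057, so ρ ≈ 0.94. No such correlation between hands is stated.

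**Power under each reading (two-sided, SD of the difference)**

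| d | Pairs | Normal formula | Noncentral t |
|---|---|---|---|
| 0.1017 | 86 | 15.5% | 15.4% |
| 0.1017 | 100 | 17.3% | 17.2% |
| 0.305 | 85 | 80.3% | 79.4% |
| 0.305 | 86 | 80.7% | 79.9% |
| 0.305 | 100 | 86.2% | 85.6% |

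For example, 0.1017 × √86 − 1.96 = 0.943 − 1.96 = −1.017, and Φ(−1.017) = 0.155. With 86 pairs, power at 0.1017 is 24% under one-sided alpha and 9.8% on the within-subject SD scale.

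The smallest effect detectable with 80% power from 86 pairs is 2.802 ÷ √86 = 0.302, about three times the printed value.

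**The case against.** The strongest defence is that the sentence is damaged, not the design. It has a closing quotation mark with no opening one, and the formula it introduces is not visible. Since 0.61 ÷ 2 = 0.305, the last division could be a garbled approximation sign with 0.3. On that reading the trial has close to its claimed power, and the missing formula may show the value used. Most of this stands, and it is why N = 100 need not change. It does not remove the contradiction. The section has just argued for a smaller effect than in the earlier studies, so a further division by 3 can be read as deliberate, and nothing else in the article corrects it.

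Three stronger readings are tempting, but the document does not support them.
- *A reader might infer that the trial really has only 15% power.* That holds only if 0.102 was the value intended, and the match at 0.305 points the other way.
- *A reader might infer that 43 proves 0.305 on the paired-difference scale.* It does not: the parallel two-arm formula at 0.61 gives 2 × 7.85 ÷ 0.61² = 42.2, also 43. That is not the design the section names, but it means that matching 43 does not establish the scale.
- *A reader might infer that 50 per group is too few after dropout, since 43 ÷ 0.85 = 50.6.* The unrounded requirement is 42.19, and 42.19 ÷ 0.85 = 49.6, so 50. The 85 pairs left from 100 give 80.3% power by the normal formula. The 79.4% reflects only the switch to noncentral t.

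**Conclusion.** Section 2.4 is wrong as written: an effect size of 0.102 and 43 per sequence are incompatible at alpha 0.05 and 80% power. On the printed value the requirement is about 380 per sequence, and the planned 86 evaluable pairs give about 15% power. These two figures assume two-sided alpha and standardisation by the SD of the within-participant difference. The incompatibility itself does not depend on those choices, because no standard variant returns 43 without an unstated correlation near 0.94.

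The likelier explanation is a misprint in the assumption, with 0.305 the value used and power of about 80%. The visible text does not settle this, so what is established is a contradiction between the assumption and the sample size, not an underpowered trial.

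**What to change.** Keep N = 100. In section 2.4, state the effect size used in the calculation, the SD that standardises it and whether alpha is one- or two-sided.

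- If the value was 0.305 on the SD of the within-participant difference: delete the division by 3, state that power is about 80% at 0.305 with 85 to 86 evaluable pairs, and say that effects near 0.10 are not powered.
- If 0.102 was intended: replace the 80% with about 15% (86 evaluable pairs; about 17% if all 100 are evaluable).

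The cost is a text correction, with no change to recruitment, design or analysis. Under the first reading the power claim is essentially unchanged; under the second it falls sharply and must be disclosed.
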